### Blinding

All study personnel except the biostatistician are remaining blind to the group assigned until after eligibility is determined. Afterward, the PIs discloses the assigned Pp code and provide their information to the appropriate RA for the assigned intervention to begin.

### Development of the SystemCHANGE™ intervention

Our previous qualitative studies of medication self-management in adults and older adults indicate environmental structure and routines are important for success [46, 47]. Strategies include maintaining routines (habits and linking medication taking with other behaviors), reminder methods (cues, alarms, pillboxes, and medication location), obtaining medications (pharmacy routines) and involving a person who supports the medication taking environment. Consequently, these strategies are incorporated into the SystemCHANGE™ intervention to enhance medication self-management which has traditionally been absent from transplant patient education [48].

SystemCHANGE™ is delivered in various formats (group versus individual) over different time frames (one time to 12 weeks), and in several locations (home versus community center) [49]. We are delivering the SystemCHANGE™ intervention in the kidney transplant recipients’ homes and over the telephone since many travel long distances to a transplant center. This delivery approach facilitates the sustainability of the intervention.

The baseline SystemCHANGE™ home visit is approximately 1 hour and 20 minutes in length. Table 1 provides an overview of the first step of the SystemCHANGE™ intervention delivered during the home visit. During the second step, which is delivered over the telephone 2 weeks after the home visit, the RA and Pp recount the Pp’s discussion with the important person(s) and the selected environmental solution identified during the home visit. The RA asks the Pp to identify a date to implement the solution and encourages the Pp to continue using the electronic medication monitor. They schedule a time to speak by telephone in 1 month to review the electronic medication monitor report and evaluate progress.

**Table 1 Tab1:** SystemCHANGE^TM^ Intervention-home visit

Topic	Content
Introduction of SystemCHANGE^TM^	Overview-challenges of medication taking (takes time, not your fault, should not have to try harder, medications should be in the right place at the right time, habits and routines are key to success), focus on routines and conducting small experiments to improve medication taking, review 4 steps of SystemCHANGE^TM^, and discuss how RA will guide Pp through the process of improvement.
Review of electronic medication self-monitoring report	RA guides Pp’s review of MEMS report details; Pp’s personal MEMS report reviewed from screening phase.
Goal setting	RA discusses Pp’s medication taking goals; encouraged to have goal of 100 % medication adherence.
Determining Process Owners	RA assists Pp in identifying important people in medication taking process using Important People worksheet.
Lifestyle Routines	RA assist Pp in identifying lifestyle routines using the Life Routines worksheet.
Cycles	RA assists Pp in identifying cyclical nature of daily, weekly and monthly routines using the Cycles worksheet.
Possible Solutions for Change	RA and Pp collaboratively consider possible environmental changes to enhance medication taking routines. Participant scores ideas on Possible Solutions Scale.
Storyboard	RA encourages Pp to post MEMS report as a storyboard for success.

During the next phase of the study, step 3, medication taking goals and the “small experiments” are evaluated. This occurs each month during a telephone call by the RA to the Pp. The RA mails the electronic medication monitor report to the Pp prior to the call during which the RA asks the Pp “Tell me what you are learning about medication taking. How to you think changes you have made to routines are changing your medication taking? Tell us about any other changes to medication taking routines that you feel need to be made.” If adherence is the same or worse as before, the RA encourages the Pp to try another solution from the Possible Solutions list completed during the home visit. If medication taking is improving, the RA encourages the Pp to continue that approach. The RA reminds the Pp to share progress through a storyboard by displaying the electronic medication monitoring reports in a prominent location, such as the refrigerator.

After month 6 of the intervention phase, the RA closes the intervention by discussing the Pp’s improvements. The RA encourages the Pp to continue using the electronic medication monitor and diary for the next 6 months during the maintenance phase.

### Attention-Control intervention

The 6-month attention-control intervention involves a home visit and monthly phone calls at the same intervals as the intervention group (at attention-control months 1, 2, 3, 4, 5, and 6). Rather than the SystemCHANGE™ intervention, the attention-control Pps receive educational materials developed by the International Transplant Nurses Society that address healthy living after transplant [50]. The RA calls Pps at 1, 2, 3, 4, 5 and 6 months to review the brochure information and answer any questions about it. Time, interval, frequency, and setting are all exactly the same for the intervention and control groups. If attention-control Pps raise questions about medications or medication-taking, the RA directs them to discuss them with their transplant team contact person.

At the end of month 6 of the intervention phase, the RA closes the control by discussing the healthy post-transplant information the Pp reviewed during the previous 6 months. The RA encourages Pps to continue using the electronic medication monitor and diary for the next 6 months during maintenance phase.

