## Design

This is a 4-year, two-center, randomized controlled trial, that is single-blind (participants [Pps]) and uses a stratified sample block design with repeated measures. We are comparing the SystemCHANGE™ intervention to the attention control intervention in adult kidney transplant recipients with existing medication nonadherence documented by electronic monitoring. The repeated-measures design provides longitudinal data regarding medication nonadherence which allows us to determine when the intervention becomes effective (to determine if a lower dose of SystemCHANGE™, e.g. shorter time of delivery, is possible). It also allows us to track possible decay in medication nonadherence over time following the intervention.

We are examining the experimental effect on the outcome variable MA. During the 3-month screening phase, all Pps are using electronic monitoring to document medication taking. Those who are adherent (MA rate of .85 % or greater) exit the study. To prevent the “ceiling” effect, those with documented medication nonadherence (MA rate of less than .85 %) are stratified by low (<70 %), and moderate (70-84 %) nonadherence, based upon our previous medication nonadherence pattern research [41]. They then enter the intervention phase of the study and are randomized into either the treatment (SystemCHANGE™ intervention) or the attention control group (attention control condition). During the 6-month intervention phase, all Pps receive a home visit at baseline plus six telephone calls (at intervention months 1, 2, 3, 4, 5, 6). In addition, Pps randomized into the SystemCHANGE™ intervention are also guided in implementing SystemCHANGE™ activities related to medication taking by the Research Assistant (RA). Control group Pps receive RA-provided education guided by healthy living patient educational materials. The maintenance phase begins after the intervention and runs for an additional 6 months. This phase examines how Pps maintain MA in the absence of an intervention; however, we are continuing to use electronic monitoring to measure the outcome variable. Health outcome and healthcare cost data are collected during the intervention and maintenance phases.

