Both intervention and attention-control groups use MEMS for 6 months after the 3-month screening phase. This length of time allows adequate time to capture changes in medication-taking behavior [56]. One twice-daily prescribed medication are monitored because previous research has indicated that monitoring a second medication does not provide additional MA information [53]. The monitored immunosuppressive medication is randomly selected by the RA. Random selection of the monitored immunosuppressive medication occurs as follows: The RA numbers all of the twice-daily administered immunosuppressive medications on the Demographics Form. Most Pps will take two immunosuppressive medications twice daily. In this case, the RA will flip a coin to determine which medication will be placed in the MEMS bottle. In the event that the patient has greater than two immunosuppressive medications taken twice daily, the RA will enter the number into a random numbers generator and have the Pp monitor the randomly selected immunosuppressive medication.

Pps are trained on use of the MEMS cap by the RAs. They are instructed to only remove the randomly selected immunosuppressive medication from the MEMS cap and bottle. If a pillbox is used for medications, colored disks/“Tic-Tacs” are placed in the pillbox to remind the Pp to ingest the medication from the MEMS bottle. During the screening phase, at weeks 1 and 8, the RAs telephones the Pp to ask if they are using the MEMS and MEMS diary and if they have any questions about using them. Those Pps who do use a pillbox are asked if they are using the “Tic-Tacs” to remind them to ingest from the MEMS bottle. If there are any deviations from the procedure, the RAs will re-train the Pps.

Beginning the day after the intervention Pps are instructed how to use the cap. Cap openings will be recorded and a cumulative medication taking record generated. This record is sent to the SystemCHANGE™ intervention Pps and reviewed with them at baseline and months 1, 2, 3, 4, 5, and 6. These reports contain a summary report with graphic representation of individual bottle openings and closings within the established time window of +/-1.5 hours, the hours elapsed since the previous opening, missed doses, and drug holidays. The attention-control intervention group will continue to use the MEMS but will not be sent a report since this is the “Study” step of the SystemCHANGE™ intervention.

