### Statistical analysis

Sample size and power calculations are based on comparing expected change in medication adherence rate of patients in each group at six months - an expected adherence mean difference of 10 % based on our pilot study findings and the literature. We use an alpha of .05 and provide for 90 % power to detect indicated effect sizes in this two-arm randomized study. An effect size difference of 70 % is based on a conservative estimate of our pilot work. A sample size of 46 older KT recipients per group (final total sample 92) will meet these assumptions and provide sufficient power. Recruitment and retention rates are calculated from our pilot study, other adherence studies at the same sites, and are documented in one similar RCT adherence study in older KT recipients [63, 64]. We selected an adherence rate of 85 % to divide the adherers from the non-adherers based upon our preliminary work describing 4 clusters of KT medication adherers: those who (1) take medications on time (1.0-.85 MA rate), (2) take medications on time with late/missed doses (.84-.70 MA rate), (3) rarely take medications on time and who were late with morning and/or evening doses (.69-.20 MA rate), and (4) missed many doses (<.20). Even minor deviations in dosing adherence lead to poor outcomes, though no studies have determined the criterion adherence “dose” that distinguishes good and poor outcomes.

Appropriate descriptive analyses will be performed to examine distributional characteristics for collected measures, as well as to summarize changes over time as a function of group assignment. During this initial phase, we will explore bivariate relationships among primary and secondary outcome measures and variables thought to affect medication adherence. In addition, we will conduct analyses to determine whether the randomly assigned groups are equivalent at the start of the study on the demographic and other measures collected at baseline. Before hypothesis-testing analyses are conducted, exploratory analyses will be performed to examine the effect of various mediators and moderators on the relationship between intervention, adherence, and clinical outcome. The results of these analyses will determine what additional variables will be incorporated in the subsequent hypothesis testing (e.g., analysis of covariance).

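### As written, the SystemCHANGE arm has a telephone session at week 2 that the control schedule lacks, so the claimed exact matching of contact does not hold

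*Protocol article*

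**What the plan says.** All places are in the protocol article.

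- **Design**, both arms: "all Pps receive a home visit at baseline plus six telephone calls (at intervention months 1, 2, 3, 4, 5, 6".
- **Attention-Control intervention**, control arm: a home visit, then "The RA calls Pps at 1, 2, 3, 4, 5 and 6 months to review the brochure information". The section then says of the two arms: "Time, interval, frequency, and setting are all exactly the same for the intervention and control groups".
- **Development of the SystemCHANGE™ intervention**, SystemCHANGE arm, step 2: "During the second step, which is delivered over the telephone 2 weeks after the home visit". In this session the research assistant and participant go over the talk with the supportive person and the chosen solution, and fix a start date. It closes with an appointment: "They schedule a time to speak by telephone in 1 month to review the electronic medication monitor report and evaluate progress".
- **Same section**, step 3, evaluation of the small experiments: "This occurs each month during a telephone call by the RA to the Pp".
- **Primary outcome - medication adherence**, SystemCHANGE arm: the monitor record is "reviewed with them at baseline and months 1, 2, 3, 4, 5, and 6".

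No section gives the control arm a contact at week 2.

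**The concern.** An attention control is there to separate what is said from the fact of being contacted. The article claims that separation in strong terms, while its own account of the SystemCHANGE steps includes a contact that neither the common schedule nor the control schedule contains.

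The timing gives the point its weight. The secondary aim asks when the intervention starts to work and whether a shorter delivery would do. Its analysis uses monthly adherence from month 1. The Discussion adds that the pilot suggested an immediate effect, and it would use confirmation of this to support quick delivery in hospital or clinic. If the arms separate in the first month, one additional nurse call in that month is a competing explanation. The Background names forgetting as the commonest barrier to adherence, so a reminder effect of contact is plausible. At the week-2 session the participant is also encouraged to keep using the electronic monitor, which is the instrument that measures the primary outcome.

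**Working it through.** No modelling is needed. The check is a count of the contacts listed for each arm.

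**The plan's own figure.** Calls at months 1, 2, 3, 4, 5 and 6 make six. This reproduces the count in the Design section and matches the control schedule.

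**Is the week-2 session one of those six?** It has its own content and comes before any monthly review of the monitor report. It ends by booking a later call for that review. The monthly calls are described as a separate step, and report reviews are fixed at baseline and at each of months 1 to 6. On the text, the week-2 session is therefore additional.

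**Count as written:**

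| Contact | SystemCHANGE | Control |
|---|---|---|
| Home visit | 1 | 1 |
| Call at week 2 | 1 | 0 listed |
| Calls at months 1 to 6 | 6 | 6 |
| **Calls** | **7** | **6** |
| **All contacts** | **8** | **7** |

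- Calls: 7/6 − 1 = 0.167, or 17 % more.
- Contacts: 8/7 − 1 = 0.143, or 14 % more.
- First interval after the home visit: 2 weeks for SystemCHANGE, 1 month for control.

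Frequency and interval therefore both differ between the arms.

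**A second loose end.** If the one-month appointment runs from the week-2 session, the first report review falls at about week 6. That conflicts with the review fixed at month 1.

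**Sample size.** The point does not touch it. The plan states: "We use an alpha of .05 and provide for 90 % power to detect indicated effect sizes in this two-arm randomized study". Reading its effect size as a standardised difference of 0.70 and alpha as two-sided (sidedness is not stated), a t-test needs 43.87, so 44 per group. Dividing 43.87 by the Mann-Whitney efficiency 3/π gives 45.94, so 46, which is the planned number.

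**The case against.** The strongest reply is that this is a conflict of wording in a condensed article. Two sections describe a common schedule, and the Treatment fidelity section refers to a detailed procedure manual that is not shown. A matching week-2 control call may exist and simply not be listed. That possibility stands, so the documents do not show that controls went without one. It does not rescue the text: if the call exists, the control schedule and the six-call count are both incomplete.

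A second reply is that one call is little, and that it is itself a SystemCHANGE step with its own task, not mere attention. This also stands in part. The primary comparison is made at the end of the intervention and maintenance phases, months 6 and 12, and nothing in the documents shows that a week-2 call would still matter then. The bearing is mainly on the earliest of the 12 monthly measurements.

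A third reply is that the Fidelity Protocol Checklist already records number, duration and spacing of sessions at every encounter. That is correct. An unmatched call would be on record, and no new data collection is needed.

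A reader might infer more than the text supports in three ways:

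- **That all SystemCHANGE calls run about two weeks out of step with the control calls.** The month 1 to 6 schedule in the Design section and the fixed report reviews speak against this.
- **That SystemCHANGE participants get twice the telephone attention in month 1.** Two calls against one is a count. No call duration is given for either arm, so nothing follows about time.
- **That the monitor reports sent only to SystemCHANGE participants are part of the mismatch.** The article declares them a component of the intervention.

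**Conclusion.** The contradiction is in the text. As written, the SystemCHANGE arm has one more call than control, placed in the first month, and the stated exact equality of interval and frequency fails. This rests on taking the week-2 session as additional to the monthly calls, which is what the described steps and report reviews indicate, and on the control arm having no contact beyond those listed.

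The consequence is limited. It would be wrong to infer that the trial's main comparison is compromised: the randomised comparison of SystemCHANGE with the control package remains valid at months 6 and 12. What cannot be claimed on the present text is that an early difference comes from content rather than contact, and this matters chiefly for the secondary timing aim. The documents offer no basis for putting a number on the possible bias. The point should be settled because exact matching is a stated property of the design and is cheap to restore or to correct.

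**What to change.** Reconcile the Design section, the steps in the section on developing the intervention, the Attention-Control section and the report-review dates under the primary outcome into one contact calendar covering both arms. The calendar should say whether the week-2 session is additional and from which date the one-month appointment runs. Then take one of two routes.

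1. **Match the contact.** Add, or state if it already exists, a week-2 call for controls using the brochure material already in use. At 46 controls and one call each, this is about 46 short calls by the existing research assistants, plus a wording amendment.
2. **Correct the claim.** Withdraw the statement of exact equality and correct the six-call count. Report number and duration of contacts by arm from the existing Fidelity Protocol Checklist, and interpret any early separation of the arms with that caveat. This costs only wording and a table, but leaves the early attribution question open.

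The first route is preferable if participants are still to enter the intervention phase. The second remains available in any case. Neither changes the sample size.

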### Treatment fidelity

A detailed procedure manual provides specific information about every facet of the interventions. To ensure RA fidelity to the intervention and control arms, a Fidelity Protocol Checklist is used during all Pp encounters where key elements of the protocol are documented including number of intervention sessions, session duration, length of time between sessions, and intervention steps (e.g. greeting the Pp, MEMS review, use of intervention forms). Each element is rated as completed, partially completed, not completed, or N/A. Field notes are documented for every encounter, which could include Pp’s body language, environmental issues (e.g. temperature, noise), and presence of others in the home. Field notes for telephone contacts include background noise, telephone line distortion, and any difficulty hearing by RA or Pp.

### Training the research assistants who deliver the intervention

An expert in SystemCHANGE™ delivers content training to RAs who are baccalaureate-prepared RNs at the study recruitment sites. To preserve intervention integrity, simulation and role play are used until the RAs are applying the protocol consistently, as judged by the expert using the SystemCHANGE™ protocol checklist. In addition to teaching RAs SystemCHANGE™ principles and steps, the expert guides RAs as they practice using the study protocol and protocol checklist on a sample of Pps. To ensure the highest level of RA protocol knowledge and skills, training sessions also include role playing of disruptive situations for both interventions, and delivering both intervention for a different behavior change such as exercise or diet. SystemCHANGE™ RAs are trained separately from the control RAs. The expert provides RAs feedback on performance, and RAs retrain as necessary until they have achieved 100 % intervention protocol integrity.

### Primary outcome - medication adherence

Table 2 provides an overview of study measures and outcomes. The MA calculation method has been previously described but will be briefly described here [41]. A 0.5 is assigned if the dose of the immunosuppressive medication is taken within a 3-hour window (+/-1.5 hours of the prescribed time); 0.25 is assigned if the dose of the immunosuppressive medication is not within the 3-hour window but is taken within a 12-hour window (+/-6 hours of the prescribed time), and 0 is assigned if the dose of the immunosuppressive medication is not taken within a 12-hour window (+/-6 hours of the prescribed time, i.e., if the dose was missed). On each day, an individual is assigned a score of 0, 0.25, 0.50, 0.75 or 1 points (p. 526).

**Table 2 Tab2:** Study outcomes and measures

	Screening	Intervention	Maintenance
*Inclusion Criteria*			
6-item telephone measure of cognition	√		
Primary Outcome			
Medication adherence–electronic medication monitoring	√	√	√
Secondary Outcomes			
Creatinine	√	√	√
Blood urea nitrogen	√	√	√
Acute rejection	√	√	√
Chronic rejection	√	√	√
Infection	√	√	√
Death	√	√	√
*Potential Mediators*			
Social Support		√	√
Perceived Health		√	√
Personal Systems Thinking		√	√
*Background*/*Moderating Variables*			
Medical History	√		
Demographics (ethnicity)	√		
Level of Medication Nonadherence	√		
Pillbox use	√		
*Health care costs*			
Hospitalizations, clinic, observation, and ER visits	√	√	√

The primary outcome is medication adherence measured by the MEMSCap™ Medication Event Monitoring System SmartCap® (WestRock, USA & Switzerland). The system is comprised of two parts: a standard plastic vial with a threaded opening and the SmartCap® which has an LCD readout that displays the number of doses taken in the past 24 hours and the hours elapsed since last dosing. A micro-electronic circuit in the SmartCap® registers the date and time when the top is opened and closed to create a medication “event”. Time-stamped medication events stored in the MEMS® 6 can be transferred at any time through the MEMSCap™ Wireless Reader to medAmigo. The medAmigo portal is a web-based application used to securely download and centrally store medication dosing history (www.medAmigo.com). MedAmigo performs the MA score calculations. Although no gold standard measure exists for MA, most researchers consider electronic monitoring caps the best method. It is the only adherence measure that can accurately assess this variable, as recall memory is unlikely to be accurate enough for self-reports to provide valid data regarding the exact timing of doses over a period of time. The batteries for the MEMS 6 have a 36 month life and can store up to 3800 medication events. This battery life has been shown to be more than sufficient for capturing 12 months of medication taking activity [51]. The MEMS has been shown to be reliable in temperatures from -20 °C to 70 °C and in up to 95 % humidity [52], are accurate to within 2 minutes per month, and have a reported 2 % failure rate [52, 53]. The ability of electronic monitoring to provide a precise assessment of dosage timing is particularly advantageous as studies are beginning to emerge that reveal the importance of the interval between doses in explaining the relationship between adherence and clinical outcomes in other chronic illnesses [54, 55].

Both intervention and attention-control groups use MEMS for 6 months after the 3-month screening phase. This length of time allows adequate time to capture changes in medication-taking behavior [56]. One twice-daily prescribed medication are monitored because previous research has indicated that monitoring a second medication does not provide additional MA information [53]. The monitored immunosuppressive medication is randomly selected by the RA. Random selection of the monitored immunosuppressive medication occurs as follows: The RA numbers all of the twice-daily administered immunosuppressive medications on the Demographics Form. Most Pps will take two immunosuppressive medications twice daily. In this case, the RA will flip a coin to determine which medication will be placed in the MEMS bottle. In the event that the patient has greater than two immunosuppressive medications taken twice daily, the RA will enter the number into a random numbers generator and have the Pp monitor the randomly selected immunosuppressive medication.

Pps are trained on use of the MEMS cap by the RAs. They are instructed to only remove the randomly selected immunosuppressive medication from the MEMS cap and bottle. If a pillbox is used for medications, colored disks/“Tic-Tacs” are placed in the pillbox to remind the Pp to ingest the medication from the MEMS bottle. During the screening phase, at weeks 1 and 8, the RAs telephones the Pp to ask if they are using the MEMS and MEMS diary and if they have any questions about using them. Those Pps who do use a pillbox are asked if they are using the “Tic-Tacs” to remind them to ingest from the MEMS bottle. If there are any deviations from the procedure, the RAs will re-train the Pps.

Beginning the day after the intervention Pps are instructed how to use the cap. Cap openings will be recorded and a cumulative medication taking record generated. This record is sent to the SystemCHANGE™ intervention Pps and reviewed with them at baseline and months 1, 2, 3, 4, 5, and 6. These reports contain a summary report with graphic representation of individual bottle openings and closings within the established time window of +/-1.5 hours, the hours elapsed since the previous opening, missed doses, and drug holidays. The attention-control intervention group will continue to use the MEMS but will not be sent a report since this is the “Study” step of the SystemCHANGE™ intervention.

Participants mail the MEMS diary to the RA to document any accidental cap openings, openings when no medication was ingested, (e.g. when refilling MEMS bottle), and early openings when a medication was removed early to be administered later (pocketing a dose), but on time, (e.g. clinic appointments). As in our preliminary work, we will correct MEMS cap data using the MEMS diary. The diary successfully corrects any invalid data from MEMS opening when medications were not ingested or were ingested at a time different from the time the MEMS was opened [57]. After these corrections, we assume that each cap removal represents the patient ingesting one dose of the prescribed immunosuppressant. To enhance accuracy, Pps are trained on use of the MEMS diary. Pps are given specific examples of when the diary should and should not be used. They are trained to store the diary with the MEMS bottle. Training continues until the Pp achieves 100 % accuracy using the MEMS diary with 4 MEMS diary test scenarios (i.e., accidental opening, early opening [pocketing dose], opened but no medication administered, and diary storage). This approach to using a MEMS diary to correct adherence data has been validated in several previous research studies [19–43, 53, 57].

